### Random allocation and concealment of allocation

The random assignment sequence was created using EPIDAT, 3.1 statistical software, which stratifies the patients according to lymphedema stage, with a 1:1 ratio, using blocks having a random size of 4. The assignment sequence was hidden from the researcher assessing the participants through sequentially numbered envelopes that are opaque, sealed and stapled.

Allocation will be carried out by a department specialist in the Physical Medicine and Rehabilitation department.

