### Study variables and measurement instruments

The study variables are shown in Tables 1, 2, 3.

**Table 1 Tab1:** Independent study variables and their measurement instruments

INDEPENDENT VARIABLES (Sociodemographic and clinical variables)	MEASUREMENT INSTRUMENTS (to be filled in with information from interviews and clinical records)
- ID: Identification number for the study (1, 2, 3...)	ID:
- Age.	Date of bird _/_/_ _ years old
- Group (Treatment carried out):	TAPA / standard.
- Work activity:	Working (Which?) /Retired/Unemployed/Others (Which?)
- Menstrual situation:	Pre-menopausal/Post-menopausal
- Laterality:	Right/ left/Both
- Body mass index (BMI): - Obesity:	BMI: height/weight^2^ yes (BMI > =30)/ no (BMI < 30)
- AHT (Arterial hypertension):	Yes (> = 120/80 mmHg/take medication) / no (< 120/80 mmHg)
- DLP (Dyslipidemia):	Yes (> = 200 mg dl/take medication) / no (< 200 mg/dl)
- DM (Diabetes):	Yes (> = 126 mg dl/take medication) / no (< 126 mg/dl)
- Heart disease:	Yes / no
- Kidney failure: Yes / no	Yes / no
- Vascular disease: Yes /no	Yes / no
- Thyroid disease: Yes / no	Yes / no
- Pacemaker: Yes / no	Yes / no
- Electro-stimulator: Yes /no	Yes / no
- Date of BC diagnosis	_/_/_
- Date of lymphedema diagnosis	_/_/_
- Stage:	I, II
- Edema location:	Hand(H)/Forearm (F)/Arm (A)/ Breast H + F/ H + F + A/ F + A/ Complete/ Others (this category should be thoroughly considered)
- Breast:	Right/ left
- Date of surgical intervention:	_/_/_
- Type of tumor: - Intervention type: Conservative/mastectomy	ductal infiltrating/in situ/ lobular/ inflammatory/tubular/other (which?): Conservative/mastectomy
- Axillary surgery:	sentinel ganglion biopsy (SGB)/ lymphadenectomy /Both/none
- No. of excised ganglia:	N°
- No. positive ganglia:	N°
- Complications:	Infection/ hematoma/ seroma/nerve lesion/Axillary web syndrome
- Chemotherapy:	Yes / no
- Radiotherapy:	Yes / no
- Hormone therapy:	Yes / no
- Immunotherapy:	Yes / no
- Breast reconstruction:	Yes / no Yes: - Type of reconstruction: Prosthesis/back/ abdomen - Reconstruction time: Immediate/ deferred
- Date of symptom onset:	_/_/_
- Lymphedema:	Right/ left

**Table 2 Tab2:** Primary dependent study variables and their measurement instruments

PRIMARY DEPENDENT VARIABLES	MEASUREMENT INSTRUMENTS/INTERPRETATION OF RESULTS

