### Statistical analysis

Analysis is performed for intent to treat. Data lacking after the basal measurements are replaced using the last available observation. Quantitative and qualitative variables will be described as usual (mean, standard deviation; proportions). An analysis of basal comparability of the sociodemographic and clinical variables **(**Table 1**)** will be carried out between both treatment groups. Then, a bivariate analysis will be conducted, previously verifying that the quantitative variables follow a normal distribution, using the Kolmogorov-Smirnov or Shapiro-Wilk tests, in which case, a repeated measures ANOVA is carried out (Mixed Models), to analyze the profile of patients from the basal measurement (24–72 h before treatment onset), after completing 10 sessions and one and 3 months later. If the variables do not follow a normal distribution, non-parametric tests will be used (Friedman’s test). In addition, a multivariate analysis will be performed, as well as a survival analysis, Cox regression or multiple linear regression, taking into account the examined sociodemographic and clinical covariables resulting statistically significant following the bivariate analysis, for their inclusion in the model or to be controlled for, given their potential confounding effect. The main dependent variable will be the reduction of volume of the affected extremity. Statistical analysis will be performed using the Statistical Package for the Social Sciences (SPSS v.17). Statistical significance values will be those normally used (*p* < 0.05) and bilateral contrasts will be carried out. To evaluate effectiveness, a comparative analysis of economic costs of both treatments will be performed.

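### The adjusted model chooses covariates by bivariate significance, so stage, the randomisation stratum, is adjusted for only if it happens to be significant, and no model fixes baseline volume as a covariate

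*Protocol article*

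**What the plan says.** The Statistical analysis section of the protocol article sets out three steps.

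- First comes a comparison of the arms at baseline: "An analysis of basal comparability of the sociodemographic and clinical variables" of Table 1.
- Next is a bivariate analysis. This is a repeated measures ANOVA or mixed model over four visits (baseline, after 10 sessions, and 1 and 3 months later), or Friedman's test if normality fails. No covariate screening applies here.
- Then: "In addition, a multivariate analysis will be performed, as well as a survival analysis, Cox regression or multiple linear regression". This model takes in the sociodemographic and clinical "covariables resulting statistically significant following the bivariate analysis, for their inclusion in the model or to be controlled for", and the reason given is possible confounding.

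The general significance level is p < 0.05, "and bilateral contrasts will be carried out". No separate screening threshold is given. The main dependent variable is the reduction in volume of the affected limb.

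The candidates are in Table 1, headed "INDEPENDENT VARIABLES (Sociodemographic and clinical variables". Stage is one of them. Under Random allocation and concealment of allocation, the software is one "which stratifies the patients according to lymphedema stage, with a 1:1 ratio". Under Interventions, stage also determines what the control arm receives. Baseline volume is not in Table 1; it appears only as the first time point of the repeated measures analysis.

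**The concern.** In a randomised trial, differences between arms at baseline arise by chance, so a significance test does not identify a confounder. Screening covariates against the outcome makes the model depend on the data. The article does not say which of these two meanings of significant applies, so two analysts could follow it and fit different models.

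Stage is where this matters most. A stratification factor belongs in the analysis by design, and here it also defines the comparator. Under the stated rule it has no more standing than any other Table 1 item.

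The model type is open as well. Survival and Cox methods are offered beside linear regression, although no event is defined and volume is measured at scheduled visits.

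What is at stake is the adjusted treatment effect: its size, its precision, and whether it can be reproduced from the plan. The article does not say whether the repeated measures analysis or the multivariate model is primary, so the screened result could become the headline.

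**Working it through.** **Inputs from the protocol article.** Sample size: reductions of 20% and 5% (difference 15), SD 20, alpha 0.05, power 0.80, 29 per group, 64 in total. Randomization: stratified by stage, 1:1, blocks of 4. Statistical analysis: p < 0.05, two-sided.

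**The plan's own figure.** n per group = 2(1.96 + 0.84)² × (20/15)² ≈ 27.9, so 28 by the normal approximation. The t-test version gives 28.9, so 29, as stated (power 80.1%). Then 29 × 1.10 = 31.9, or 32 per group and 64 in total. This point does not affect the sample size.

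**Candidate count.** Table 1 lists 36 items, counting BMI and obesity separately and likewise tumour type and intervention type. Removing ID and group leaves 34. Adding the two reconstruction sub-items gives 36; merging near-duplicates (BMI with obesity, the several side variables) gives about 30.

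**Chance selection.** Assume all m candidates are null and independent. Expected selections = 0.05m; chance of at least one = 1 − 0.95^m.

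| m | Expected | At least one |
|---|---|---|
| 30 | 1.5 | 78.5% |
| 34 | 1.7 | 82.5% |
| 36 | 1.8 | 84.2% |

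**Effect on the treatment estimate.** I used a simulation of 5,000 trials per setting: 64 patients, 34 candidates, stage-stratified blocks of 4, SD 20, true difference 15, and one outcome per patient. Candidates were screened at p < 0.05 without regard to arm. The documents give no prognostic correlations, so those for baseline and stage are assumed. Each cell gives mean estimate and power.

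| Correlation: baseline, stage | Fixed adjustment | Screened on outcome | Screened on arm imbalance | Stage selected (outcome screen) |
|---|---|---|---|---|
| 0, 0 | 15.0, 83.6% | 13.6, 78.1% | 15.0, 78.1% | 4% |
| 0.3, 0.2 | 15.1, 88.8% | 13.7, 83.3% | 15.1, 80.2% | 31% |
| 0.5, 0.3 | 14.9, 95.0% | 14.0, 92.0% | 14.9, 79.5% | 64% |

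The power lost by outcome screening is 83.6 − 78.1 = 5.5, 88.8 − 83.3 = 5.5 and 95.0 − 92.0 = 3.0 points. The estimate shrinks because a covariate that is unbalanced between arms by chance borrows the treatment effect, looks prognostic, is selected, and then absorbs part of that effect. Screening on imbalance leaves the estimate unbiased but loses precision.

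With a true difference of 0, the rejection rate was 5.2%, 5.1% and 4.4% under outcome screening, and 5.1%, 4.3% and 3.9% under imbalance screening. There is no inflation.

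One simplification favours the screened rule: the simulation put baseline in the candidate pool, where it could be selected. Under the article's wording it is not a candidate.

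**Gain from baseline as a covariate.** At a single follow-up visit with equal variances, a change score has variance proportional to 2(1 − ρ) and the baseline-adjusted analysis 1 − ρ². The ratio is (1 + ρ)/2. With ρ assumed to be 0.5, 0.7 or 0.9 it is 0.75, 0.85 or 0.95, so variance is 25%, 15% or 5% lower.

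**The case against.** The strongest reply is that the screened model is supplementary. The repeated measures analysis comes first, is not screened, and already uses baseline volume as its first time point. That stands. A reader might infer that the trial's whole treatment effect depends on the screen; the article supports this only for the adjusted effect.

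A reader might also infer that p-values for treatment become invalid. The simulation does not show that, since type I error stayed at about 4% to 5%. Nor do about 1.7 spurious covariates among 64 patients demonstrate overfitting.

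Baseline volume is not in Table 1, so it is not at the mercy of the screen. The issue is that no model names it as a covariate. The documents offer no evidence on how strongly it predicts outcome, and at ρ = 0.9 the gain over a change score is only 5%. That formula also fits a four-visit analysis only loosely.

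The Table 1 items are plainly not independent, so the 78% to 84% is illustrative. Under the strongest assumed correlations, the outcome-screened model (92.0% power) beat an unadjusted one (84.6%), though it stayed below fixed adjustment.

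The baseline comparability step is not stated to use significance tests or to drive adjustment; selection is tied to the bivariate analysis.

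Finally, a condensed article may leave an event definition to the full protocol or SAP, so the mention of Cox regression is not in itself an error. The selection rule is different: it is written out, and a fuller document would have to reverse it rather than complete it.

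**Conclusion.** The point holds for the adjusted model. Its covariates are chosen by significance from about 34 candidates, and stage, which is both the stratum and the determinant of the comparator, is not guaranteed a place. No model fixes baseline volume as a covariate.

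The cost is moderate. If the screen is on the outcome, the estimate is about 1.0 to 1.4 below a true 15, and power is about 3 to 6 points below fixed adjustment. If it is on arm imbalance, the estimate is unbiased with power of about 78% to 80%. These figures rest on the assumed correlations, independent candidates and a single outcome visit. The gain from baseline adjustment depends on a correlation the documents do not give.

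Invalid treatment p-values, overfitting and a fully screened primary analysis are not supported. This is a rule worth replacing, not a flaw that undermines the trial.

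**What to change.** In the Statistical analysis section:

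- Include lymphedema stage and the baseline value of the outcome as prespecified covariates in the treatment-effect model, regardless of significance.
- Drop the bivariate-significance rule for the treatment effect.
- Label any further covariate-adjusted model a sensitivity analysis, with its covariates named in advance.
- Use a linear or mixed model for volume reduction. Keep survival or Cox analysis only if an event is defined.

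The cost is wording alone. Stage and baseline volume are already collected, and neither the sample size nor the visit schedule changes.

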### Interventions

Following capture and recruitment, participants were randomly assigned to one of the two groups.

Both groups will receive a 3-h long healthcare education workshop on lymphedema (Lymphedema workshop), led by a department specialist in the Physical Medicine and Rehabilitation Dept. of the Clinical Inter-level Rehabilitation Management Area (MV), and offering basic knowledge on the physiopathology of lymphedema, identification of symptoms, preventive skin care measures, ADL orientation, including physical activity and recommendations for neck and arm anti-edema exercises and postures to be carried out at least once daily.

The interventions used for the Experimental group will be the same for stage I and II, and will receive 10 sessions (2 per week), of 30 min each, led by an Occupational Therapist from the Córdoba and Guadalquivir health district (MN):

− 10-min neuro dynamics oriented to the activity.

− 10-min proprioceptive neuromuscular facilitation activities.

− 10-min proprioceptive anti-edema bandaging, including patient and/or caretaker instructions for placement, as well as assistance on techniques to use for performing everyday activities.

Proprioceptive anti-edema bandaging will be placed after carrying out the neuro dynamic and neuromuscular facilitation activities. Cohesive elastic bandages will be used, containing a high content of cotton and anti-slip.

The Control group intervention, depending on the stage, will be led by a physiotherapist from the Reina Sofía Hospital in Córdoba, and will consist of:

Stage I:

- Preventive measures, skin care and exercise prescribed by the rehabilitation physician and training in the lymphedema workshop.

- Compression garments.

-Duration of 5 weeks.

Stage II:

Ten sessions of 60 min of conservative treatment of Complex Decongestive Therapy (the literature does not refer to specific protocols to quantify session duration, therefore, expert opinions based on everyday practice were used as a reference):

-Skin care.

-Multi-layer bandaging.

-Manual lymphatic drainage.

-Massage therapy (22).

Participants will be notified that during the intervention and follow-up period, they may not undertake other treatment for their BCRAL and, in the case of being subject to experimental treatment and not achieving the expected edema reduction, they may complete standard treatment upon study completion.

To analyze the patient profile from the basal measurement (24–72 h prior to treatment onset), until immediately following completion of the 10 sessions and one and 3 months later (Fig. 1).

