Studies have suggested the incorporation of proprioceptive neuromuscular facilitation elements (PNF) with traditional methods of manual lymphatic drainage (MLD), to facilitate the treatment process for lymphedema patients, since they induce powerful synergic effects on edema volume, range of motion (ROM) of the shoulder, pain and depression [25]. Their independent or combination use with laser treatment has also been suggested, since improvements were also found in these variables and even in the rate of blood circulation in the underarm [26]. Also, in a study in which bandaging was not used, CDT was combined with PNF and respiration, reducing the lymphedema and also improving ROM [27], which could potentially improve activity performance, participation level and thus, quality of life [14, 28].

In response to the evidence regarding the use of the Coban®3 M bandage as an early precursor to pressotherapy in the rehabilitating treatment of lymphedema to reduce prolonged edema (the causal agent of multiple complications and functional loss) [18, 29–31], we propose the possibility of testing the effectiveness of similar bandages, but ones that avoid compressive syndromes, decrease pain and edema, promote the development of ADL and improve the treatment’s cost-effectiveness [32, 33]. We suggest combining its use with the three previously mentioned techniques (healthcare education/patient training, neuro-dynamic activities geared to neuro-muscular use and proprioceptive neuro-muscular facilitation oriented towards ADL) and which, collectively, are referred to as “TAPA” (in Spanish, Activity-oriented proprioceptive antiedema therapy).

Given the consensus for conservative lymphedema treatment, such as Complex Decongestive Therapy (CDT) or Complex Physical Therapy (CPT), we believe that comparison with our TAPA treatment should be made with this type of treatment.

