### Sample size

It is agreed that a decrease in the volume of the clinically relevant lymphedema may be established at 150 ml. (minimal detectable value) [39], 20% with respect to the baseline. Based on data from the literature on means and standard deviations [25, 40], for an alpha error of 0.05 and a statistical power of 0.80, the necessary sample size would be 29 subjects per group (calculation performed with EPIDAT 4.2). It is assumed that the standard treatment effect in the control group will lead to a reduction in arm volume by an average of 5%, the treatment effect in the experimental group will cause an average reduction in arm volume of 20%, and the standard deviation will be similar in both groups, approaching 20% [41]. Taking into account the dropout rate of 10% in each group, the corrected sample size is 64 patients, randomly assigned to two groups with 32 patients each.

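### The control treatment differs by stage, but sizing and analysis treat it as one comparator, so the overall result cannot by itself support a comparison with complex decongestive therapy (CDT)

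*Protocol article*

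**What the plan says.** **Treatments (Interventions).** TAPA is identical in both stages: ten 30-minute sessions, two per week. The control is not: "The Control group intervention, depending on the stage, will be led by a physiotherapist".

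- Stage I control: "Preventive measures, skin care and exercise prescribed by the rehabilitation physician and training in the lymphedema workshop", plus compression garments, for 5 weeks. No CDT is listed.
- Stage II control: "Ten sessions of 60 min of conservative treatment of Complex Decongestive Therapy", made up of skin care, multi-layer bandaging, manual lymphatic drainage and massage.

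Both randomised groups attend the 3-hour workshop.

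**Comparator.** The Hypothesis is set against standard treatment and the Objectives against conventional treatment. The Abstract gives DLT and CPT as examples of conventional treatment. The Background, speaking of CDT and CPT, goes further: "we believe that comparison with our TAPA treatment should be made with this type of treatment".

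**Randomisation.** Allocation is 1:1 in blocks of 4, using software "which stratifies the patients according to lymphedema stage". No number or quota per stage is given.

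**Sample size.** One control effect serves the whole trial: "It is assumed that the standard treatment effect in the control group will lead to a reduction in arm volume by an average of 5" per cent. The experimental reduction is 20%, the SD about 20%, and the result is 29 per group, or 64 in total after dropout.

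**Statistical analysis.** The two treatment groups are compared by repeated measures. Sociodemographic and clinical covariables, among which Table 1 lists stage, enter the multivariate model if they are significant in the bivariate analysis. Only the cost target, under Expected results, is set against the standard treatment of the respective stage.

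**The concern.** The same TAPA programme is set against two different controls, so the trial contains two comparisons: TAPA versus garments with self-care measures in stage I, and TAPA versus CDT in stage II. A single two-group contrast returns their weighted average, and the weights are the recruited stage proportions, which the plan does not fix. If the two stage effects differ, the headline figure moves with case mix, and a positive overall result may come mainly from stage I patients, whose controls had no CDT.

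This matters because the Abstract and Background invite the result to be read as a comparison with decongestive therapy. Only stage II bears on that question.

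The covariate rule adds a second weakness. Stage governs both the randomisation and the control treatment, so its place in the model should not depend on a significance test. Stage as a main effect alone would still leave the two comparisons merged; that needs a treatment-by-stage term or separate contrasts.

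**Working it through.** **Inputs from the Sample size section:** mean reductions of 5% and 20%, hence a difference of d = 15 points; SD = 20; alpha 0.05, two-sided (Statistical analysis); power 0.80; dropout 10%. Stage mix and stage-specific effects are not in the document, so values used for them are assumptions.

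**Formula.** Two-sample t test with n per arm: noncentrality = d / (SD × √(2/n)), with 2n − 2 degrees of freedom.

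**1. The plan's own figure.** For n = 29: 15 / (20 × √(2/29)) = 2.856, critical t = 2.003, power 0.801. For n = 28 the power is 0.787. So 29 per group reproduces. 29 × 1.1 = 31.9, giving 32 per group and 64 in total, as stated. This sizes the overall contrast and nothing else.

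**2. The same 15-point effect within one stage.**

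| Evaluable per arm in the stage | Power |
|---|---|
| 8 | 0.29 |
| 12 | 0.42 |
| 14 | 0.48 |
| 15 | 0.51 |
| 16 | 0.54 |
| 20 | 0.64 |
| 29 | 0.80 |

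An even mix gives 29/2 = 14.5 evaluable per arm per stage, with power about 0.50. The 16 row is an even split of the 32 randomised, with no dropout. For 80% power against CDT alone, stage II would need 29 evaluable per arm, which is the entire planned evaluable sample.

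**3. Precision at an even mix.** Standard error = 20 × √(2/14.5) = 7.43. Half-width of the 95% CI = 2.05 × 7.43 ≈ 15.2 points, about as large as the planned effect.

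**4. Dependence on case mix (illustration only).** With stage effects d1 and d2 and stage I share w, the overall contrast estimates w × d1 + (1 − w) × d2. Take d1 = 25 and d2 = 5, with 29 per arm:

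| Stage I share | Overall effect | Power, SD 20 | Power, unadjusted, SD inflated |
|---|---|---|---|
| 30% | 0.3 × 25 + 0.7 × 5 = 11 | 0.54 | 0.50 |
| 50% | 15 | 0.80 | 0.75 |
| 70% | 19 | 0.94 | 0.92 |

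The last column applies if 20 is the within-stage SD and the 20-point gap lies in the control means. At an even mix the control variance is then 400 + 100 = 500 against 400 under TAPA, so the common SD is √450 = 21.2. In the same scenario, power for the 5-point effect against CDT is about 0.10 with either 14.5 or 16 per arm.

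**5. No benefit over CDT (illustration only).** With d2 = 0 and d1 = 15, the overall effect at a 50%, 70% or 80% stage I share is 7.5, 10.5 or 12 points. The chance of a significant overall result is 0.29, 0.50 or 0.61.

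**The case against.** **Standard care by stage is a legitimate comparator.** This stands. The Hypothesis and Objectives name standard or conventional treatment, the Abstract discloses the stage-dependent control and mentions DLT and CPT only as examples, and stratified 1:1 allocation keeps the overall comparison unbiased. A reader might infer that the overall contrast fails to answer the trial's question. The documents do not support that: it answers the question in the Hypothesis and Objectives. What it cannot carry alone is the narrower comparison in the Background, which the Abstract also suggests.

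**The article never says that the stages are pooled without stratum terms, and an unseen SAP could add stage contrasts.** Partly right: the absence of an interaction term from a condensed article would not be a finding in itself. The point rests on what the article does fix, namely a stage-dependent control, one control effect for sizing, and a significance rule for clinical covariables.

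**Stage I control is not shown to be a minimal-contact arm.** Also right. A reader might infer it because no sessions are listed for stage I. But the sentence naming a physiotherapist introduces both stages, and stage I control runs 5 weeks, the time that ten TAPA sessions take at two per week. Contact time is unspecified, not shown to be low.

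**The 25- and 5-point scenario is invented.** It is illustrative, and its power figures shift by 2 to 5 percentage points with the SD convention. It shows the mechanism and does not describe this trial.

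**Conclusion.** The point holds in limited form and should be fixed. The overall contrast is a valid estimate of TAPA versus stage-appropriate standard care. It is also a case-mix-weighted average of two different comparisons, and the plan neither fixes the mix nor secures stage a place in the model. Any conclusion about CDT must come from stage II.

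The firm numbers are that 29 per group gives 80% power for the overall contrast only, and that stage II alone would need the same 29 evaluable per arm. Under an assumed even mix, stage-specific power is about 50% for a 15-point effect, with a CI half-width of about 15 points; with 8 to 20 evaluable per arm in a stage, power runs from 0.29 to 0.64. These figures use the protocol's SD of 20 within stage.

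A reader might go further and infer that the trial plans to claim superiority to CDT. No such conclusion is written into the protocol. The risk is misattribution when the result is reported.

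**What to change.** 1. Include stage in the primary model whatever its bivariate p-value, and add treatment-by-stage.
2. Report the TAPA-minus-control difference with a 95% CI for stage I (versus garments, workshop and self-care measures) and for stage II (versus CDT), beside the stage-adjusted overall effect.
3. Describe the overall effect as versus stage-appropriate standard care, align the Abstract and Background wording with the Hypothesis and Objectives, and base any statement about DLT, CPT or CDT on the stage II contrast only.
4. State in the Sample size section that 80% power applies to the overall contrast, and give the stage-specific power under a declared stage mix.

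**Cost.** Changes to analysis wording and a narrower claim, with no extra patients, data or change in treatment. The drawback is wide stage-specific intervals. The treatment-by-stage test will be weak too: at an even mix its standard error is 20 × √(4/14.5) = 10.5 points, giving about 30% power for a 15-point difference between the stage effects. The term should therefore serve to estimate the two effects, and a non-significant interaction should not be read as evidence that they are equal.
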